### Outcome Measures

The primary outcome variable will be self-reported 30-day PPA at 3 months, operationalized as not having vaped, even a puff, in the last 30 days. The secondary measures include the intention to quit smoking in the next 6 months (*yes* or *no*), number of puffs per vaping session, number of vape sessions per day, and number of sessions in the past 30 days.

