**Objective:**

The primary aim of our study is to determine the effectiveness of the *Crush the Crave* app in supporting vaping cessation among youth recruited to the intervention arm via comparison with an assessment-only control group. The primary hypothesis is that participants in the intervention group—those using *Crush the Crave*—will be more likely to be abstinent at the 6-month follow-up point than participants in the assessment-only control arm.

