**Methods:**

A 2-arm, single-blind, parallel randomized controlled trial will be conducted over 12 months. Study invitations will be sent to 600 youth (age: 16-18 years) and young adult (age: 19-29 years) e-cigarette users and randomized between an intervention arm, which will be using *Crush the Crave* (n=300), and an assessment-only control arm (n=300) in a 1:1 ratio. The primary hypothesis is that participants in the intervention group—those using *Crush the Crave*—will be more likely to be abstinent at the 6-month follow-up point.

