### Data Collection

A baseline questionnaire will be sent to both the intervention group and the control group, using a self-administered web-based survey. This will collect comprehensive data on the history and characteristics of vaping (eg, vaping dependence, use of e-cigarettes, and self-confidence to quit), self-perceived addiction to vaping, health status (including mental health, mood, and perceived stress), and current and previous history of the use of other substances (combustible cigarettes, marijuana, alcohol, hookahs, and other tobacco products). The baseline survey will also ask questions on environmental factors and cessation goals. Self-reported demographic data (age, sex, gender and sexual orientation, province and country of residence, race and ethnicity, education, and marital status) will also be collected in the baseline survey.

A follow-up survey will be sent to the control and intervention groups at 3, 6, 9, and 12 months. Responses to the follow-up survey will be used to analyze any significant changes in vaping habits and differences between groups. The follow-up survey questionnaire includes items on cross-contamination and the use of cessation methods.

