### Data Analysis Plan

#### Primary Outcome

Demographic and vaping characteristics (eg, vaping dependence, use of e-cigarettes, and self-confidence to quit) will be compared between groups at baseline. The intention-to-treat principle will be followed for statistical analyses, and all participants will be analyzed in the study arm to which they were randomized. Negative binomial regression with an identity function and robust SEs will be used to test between-group comparisons of the primary outcome variable—30-day PPA at follow-up. Multiple imputation via chained equations using the observed predictors of outcomes and the predictors of loss to follow-up will be performed to impute missing outcome data to correct for any potential bias caused by missing data. The imputation model will include age, sex and gender, education, marital status, province of residence, ethnicity, vaping dependence, self-confidence to quit, perceived stress, and the intervention group. The inverse of the adjusted risk difference will provide the number needed to treat.

The sample size of 600 (inclusive of both the control arm and the intervention arm) was selected to differentiate an effect size odds ratio of 1.60, assuming a base cessation rate of 5%, an α of .05, a power of 0.8, and a 75% (450/600) response rate.

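### The primary outcome is set at 3 months but the primary hypothesis is set at 6 months, so the confirmatory test is not fixed

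*Protocol article*

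**What the plan says.** Outcome Measures is the only section that defines the primary outcome: "The primary outcome variable will be self-reported 30-day PPA at 3 months". Abstinence is defined there as no vaping at all over the 30-day window. The secondary measures listed there do not include abstinence at any other wave.

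The primary hypothesis appears four times, each time at 6 months. The Abstract Objective says that app users "will be more likely to be abstinent at the 6-month follow-up point than participants in the assessment-only control arm". The last paragraph of the Introduction and the Protocol Overview in the Discussion repeat this, and the Abstract Methods has a shorter form: "will be more likely to be abstinent at the 6-month follow-up point".

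The analysis section (Data Analysis Plan, Primary Outcome) describes "between-group comparisons of the primary outcome variable—30-day PPA at follow-up" and gives no month. The schedule in Data Collection is: "A follow-up survey will be sent to the control and intervention groups at 3, 6, 9, and 12 months".

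**The concern.** A confirmatory trial needs one pre-specified primary comparison. Here the outcome definition and the hypothesis point to different surveys, and the analysis wording fits either.

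Two things are at stake:

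- **Error control.** With two published candidates, a significant result at either wave could be presented as the pre-specified one. If the choice depended on the results, the nominal 5% would no longer hold.
- **The question answered.** Each wave asks about its own 30-day window, so a participant can be abstinent at one and vaping at the other. A difference at 3 months does not establish the 6-month claim. The number needed to treat, which the article derives from the adjusted risk difference, would refer to an unknown month.

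**Working it through.** **Step 1. Set the statements side by side.**

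| Place in the article | Time point for abstinence |
|---|---|
| Abstract, Objective (hypothesis) | 6 months |
| Abstract, Methods (hypothesis) | 6 months |
| Introduction, last paragraph (hypothesis) | 6 months |
| Discussion, Protocol Overview (hypothesis) | 6 months |
| Methods, Outcome Measures (primary outcome) | 3 months |
| Data Analysis Plan, Primary Outcome (test) | none given |
| Data Analysis Plan, sample-size paragraph | none given for the 5% base rate or the 75% response rate |

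The count is 6 months in 4 of 4 hypothesis statements, 3 months in the single outcome definition, and no month in the analysis or sample-size text.

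**Step 2. Look for text that would reconcile them.**

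- The 6 months mentioned in Outcome Measures is the horizon of the intention-to-quit question, not an abstinence time point.
- Abstinence at 6 months is not named as a secondary or co-primary outcome.
- No repeated-measures model, order of testing or multiplicity rule covers the waves.

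Nothing in the article resolves the conflict.

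**Step 3. Size the exposure if the wave is chosen after seeing results.** The article gives no figure to reproduce, so this is an illustration. The 5% level is from the sample-size paragraph; a two-sided test is assumed, because the article does not state sidedness. The correlation ρ between the test statistics at different waves is also assumed.

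Under the null hypothesis, the chance of at least one significant result in two tests is

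1 − P(|Z₁| ≤ 1.96 and |Z₂| ≤ 1.96), with (Z₁, Z₂) bivariate normal with correlation ρ.

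For ρ = 0 this is 1 − 0.95² = 9.75%. For positive correlation, by numerical integration:

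| ρ | Significant at 3 or 6 months, either direction | Significant at 3 or 6 months, in favour of the app |
|---|---|---|
| 0.4 | 9.3% | 4.7% |
| 0.6 | 8.8% | 4.4% |
| 0.8 | 7.8% | 3.9% |

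The single-test references are 5% for the middle column and 2.5% for the last.

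**Step 4. Worst case.** If the unspecified follow-up in the analysis section were read as any of the four waves, the same calculation with four equally correlated tests gives 16.6%, 14.4% and 11.4% at ρ = 0.4, 0.6 and 0.8.

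**The case against.** The contradiction itself cannot be argued away. The objections concern how far it reaches.

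- **Only two waves are in conflict.** The article never offers 9 or 12 months as primary, and the analysis sentence most naturally refers back to the variable defined in Outcome Measures. This stands: the four-wave figures are a worst case, and the live conflict is 3 against 6 months.
- **The two-sided figures count harm as well as benefit.** For a false claim in favour of the app, the two-wave range is 3.9% to 4.7% against 2.5%. This also stands. The relative inflation is much the same.
- **Blinding limits the opportunity.** Under Randomization, investigators and analyst stay blinded to allocation until the analysis is complete. This is partial protection: a coded arm variable still shows at which wave the arms differ, and it does not say which wave is primary. Error control is weakened rather than lost.
- **The registered protocol may name one month.** The article cites a registration that is not at hand. If it fixes the time point, the correction should follow it. The article would still be wrong somewhere, because it states both months and an unseen document naming a single month can agree with only one of them.
- **Repetition does not prove that 6 months is intended.** The 3-month sentence is the only operational definition. This is fair, and either direction of correction must remain open to the sponsor.

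**Conclusion.** The concern holds and must be fixed. The article's current text declares a 3-month primary outcome for a 6-month primary hypothesis and leaves the month out of the analysis, so the primary comparison cannot be identified from it. That conclusion rests on the text alone and needs no assumption.

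The size of the consequence is conditional. With a data-driven choice between the two waves and an assumed correlation of 0.4 to 0.8, the two-sided error rate is about 8% to 9% instead of 5%. Those figures show what the ambiguity permits; they do not imply that such a choice will be made.

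**What to change.** 1. Check the dated registration first and say in the amendment what it states about the primary time point.
2. Name one month. Following the four hypothesis statements, the default is 6 months: change the month in Outcome Measures to 6, and list abstinence at 3, 9 and 12 months as secondary. If 3 months is intended, change the four hypothesis statements and make 6, 9 and 12 months secondary.
3. Replace the unspecified follow-up in the Primary Outcome analysis section with the chosen month, and state that the number needed to treat refers to it.
4. In the sample-size paragraph, state that the 5% base rate and 75% response rate apply at that month, and revise them if they do not.
5. Date the change and make it before anyone sees outcome data by arm, coded or not. Recruitment began on March 4, 2022, so the first 3-month surveys could fall due from about June 2022. The amendment should therefore state what data had been seen when the choice was made.

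The cost is a few wording edits and a dated amendment: three places for the 6-month route, six for the 3-month route (four hypothesis statements, the analysis sentence and the sample-size paragraph), plus the list of secondary waves. Both surveys are already scheduled, so nothing changes for participants.

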### Process Measures

The mHealth (mobile health) App Usability Questionnaire [33] will be used to collect data on process measures from the intervention group. The mHealth App Usability Questionnaire collects data on the following three main constructs: ease of use and satisfaction (8 items), system information arrangement (6 items), and usefulness (7 items). Data from app analytics will also be used as process measures for the intervention group, including whether participants downloaded the intervention (*yes* or *no*), the frequency of use, the most frequently used features, and user reviews.

Qualitative interviews (n=25) will be conducted with participants in the intervention arm to gain insight on the usability and acceptability of the app. Interviews will be audio recorded and transcribed verbatim, and they will be analyzed in NVivo 12 (QSR International) by using a 6-step approach to thematic analysis, as proposed by Braun and Clarke [34].

### Data Analysis Plan

#### Primary Outcome

Demographic and vaping characteristics (eg, vaping dependence, use of e-cigarettes, and self-confidence to quit) will be compared between groups at baseline. The intention-to-treat principle will be followed for statistical analyses, and all participants will be analyzed in the study arm to which they were randomized. Negative binomial regression with an identity function and robust SEs will be used to test between-group comparisons of the primary outcome variable—30-day PPA at follow-up. Multiple imputation via chained equations using the observed predictors of outcomes and the predictors of loss to follow-up will be performed to impute missing outcome data to correct for any potential bias caused by missing data. The imputation model will include age, sex and gender, education, marital status, province of residence, ethnicity, vaping dependence, self-confidence to quit, perceived stress, and the intervention group. The inverse of the adjusted risk difference will provide the number needed to treat.

The sample size of 600 (inclusive of both the control arm and the intervention arm) was selected to differentiate an effect size odds ratio of 1.60, assuming a base cessation rate of 5%, an α of .05, a power of 0.8, and a 75% (450/600) response rate.

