*Crush the Crave* for vaping cessation was developed based on an earlier version of the app for smoking cessation [25-27]. An RCT of 1599 young adult smokers assessed *Crush the Crave* for smoking cessation and found that the 30-day point prevalence abstinence (PPA) at 6 months for the intervention condition (118/820, 14.4%) was not significantly different (odds ratio 0.82, 95% CI 0.63-1.08) from that for the control condition (132/779, 16.9%). However, the rate of abstinence was favorable when compared with the unassisted 30-day quit rates of 11.5% of young adults [28]. In addition, it was determined that 61% of the young adult smokers in the RCT were vaping. The increasing nicotine dependence and use of vapes among youth have prompted interest in developing an app for vaping cessation based on people’s experiences with *Crush the Crave* for smoking cessation. *Crush the Crave* is a tracker app that tracks the following information: the number of vape-free days and the amount of money saved since quitting vaping, as well as triggers and cravings. The app also provides the following functions: tailored supportive messages and inspirational graphic images for quitting vaping, personalized quit plans, graphic performance feedback, digital awards for achieving milestones, the reporting of vaping triggers, assistance for dealing with cravings, and links to other supportive resources that can aid in vaping cessation.

The primary aim of our study is to determine the effectiveness of the *Crush the Crave* app in supporting vaping cessation among youth recruited to the intervention arm via comparison with an assessment-only control group. The primary hypothesis is that participants in the intervention group—those using *Crush the Crave*—will be more likely to be abstinent at the 6-month follow-up point than participants in the assessment-only control arm. Our trial is currently open for recruitment. The anticipated completion date for our study is March 2024.

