### Recruitment and Enrollment

Eligible participants are youth aged 16 to 29 years who live in Canada and have used nicotine e-cigarettes in the previous 30 days. Study participants will be recruited through the Vaping Dependence Cohort—an existing panel of youth enrolled in a prospective cohort study at the University of Toronto who provided consent for recontact in future studies at the Ontario Tobacco Research Unit. This panel is comprised of a broad sample of youth who self-reported current or past regular use of nicotine e-cigarettes. The use of nicotine e-cigarettes was assessed through a question that asked respondents if they had used e-cigarettes daily, in the past week, in the past month, in the past 3 months, or in the past year and if they had ever used an e-cigarette. This cohort was designed to balance recruitment by smoking status (*ever* or *never*), e-cigarette use (*ever* or *never*), and age (16-18 years or 19-25 years). Consequently, the prevalence of smoking, e-cigarette use, and younger participants was higher than what would be expected in a simple random sample of the population. An analysis controlling for the study design elements found that the within-group characteristics of the included youth were broadly consistent with expectations, which were based on a representative sample [9].

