#### Secondary Outcomes

For comparisons between secondary continuous outcomes and continuous outcomes, a linear regression with an identity function will be used. The secondary analysis of missing information will use the following two approaches to handle missingness: (1) imputation using the baseline observation carried forward or the classification of nonresponders as vapers in accordance with the Russell standard [35] and (2) imputation using the last observation of vaping status carried forward for nonresponders.

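### The named imputation variables leave out vaping status at the other waves, baseline e-cigarette use and smoking, which may leave bias when response depends on vaping status

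*Protocol article*

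**What the plan says.** All references are to the protocol article.

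- **Data Analysis Plan, Primary Outcome.** The rule for the primary analysis is "Multiple imputation via chained equations using the observed predictors of outcomes and the predictors of loss to follow-up will be performed". The next sentence names the variables: "The imputation model will include age, sex and gender, education, marital status, province of residence, ethnicity, vaping dependence, self-confidence to quit, perceived stress". It ends by adding arm: "perceived stress, and the intervention group". The same section plans for a 75% response, 450 of 600.
- **Data Collection.** "A follow-up survey will be sent to the control and intervention groups at 3, 6, 9, and 12 months". The baseline questionnaire also records e-cigarette use and use of combustible cigarettes.
- **Data Analysis Plan, Secondary Outcomes.** There are two further approaches to missing data. The first carries the baseline observation forward or counts nonresponders as vapers. The second is "imputation using the last observation of vaping status carried forward for nonresponders".
- **Recruitment and Enrollment.** Eligible participants must "have used nicotine e-cigarettes in the previous 30 days".
- **Primary time point.** Outcome Measures says "The primary outcome variable will be self-reported 30-day PPA at 3 months, operationalized as not having vaped, even a puff, in the last 30 days". In the Introduction, by contrast, the hypothesis says that app users "will be more likely to be abstinent at the 6-month follow-up point than participants in the assessment-only control arm".

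**The concern.** The rule is sound, but the list under it leaves out what is usually the most informative variable for a missing abstinence report: the same person's report at a neighbouring wave. Baseline e-cigarette use is also absent, although the plan groups it with dependence and self-confidence to quit as a key vaping characteristic and names those two. Smoking is absent too, although it was a balancing factor in the source cohort. An analyst who follows the list would impute a missing 6-month outcome without using a 3-month report of vaping.

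If quitters answer surveys more readily than continuing vapers, and particularly if they do so more in one arm, such a model stays close to the responder-only difference. The error would pass into the risk difference and into the number needed to treat, which is its inverse.

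The fallback approaches matter here because they are the only stated check on the imputation.

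**Working it through.** **1. Collected variables against named variables.** Named: six demographic items, vaping dependence, self-confidence to quit, perceived stress and arm. Collected but not named: 30-day vaping status at the other waves, baseline e-cigarette use and smoking.

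**2. Yardstick from the plan's own inputs.** Control rate 5% and odds ratio 1.60. Odds = 1.60 × 0.05/0.95 = 0.0842, so the app rate is 0.0842/1.0842 = 7.77%, a planned difference of 2.77 points. Planned missing: 1 − 450/600 = 25%. Whether 600 is enough for that difference is a separate matter and is not used here.

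**3. Do the fallback approaches differ?** Everyone vapes at entry, so baseline abstinence is 0 for all. Carrying baseline forward and counting nonresponders as vapers therefore agree at every wave.
- Month 3: the only earlier observation is baseline, so last observation carried forward also gives 0. All three are identical, person by person.
- Month 6: last observation carried forward differs for anyone abstinent at month 3 and missing at month 6 (17 of 1,000 in one illustrative run).

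**4. Hand calculation for a 6-month outcome with no true effect.** All inputs are assumptions: 8% abstinent at month 3 in both arms; at month 6, 60% of those and 3.5% of the rest abstinent; response 75% in controls, and in the app arm 90% among month-3 quitters and 70% among the rest; named variables explain none of this.
- True rate, both arms: 0.08 × 0.60 + 0.92 × 0.035 = 0.0480 + 0.0322 = 8.02%.
- App responders: (0.0480 × 0.90 + 0.0322 × 0.70) / (0.08 × 0.90 + 0.92 × 0.70) = 0.06574/0.716 = 9.18%.
- Control responders: 8.02%. Spurious difference 1.16 points; 1.16/2.77 = 42% of the planned difference.
- With month-3 status in the model and known for everyone, the bias is zero, because within each month-3 group response is unrelated to month-6 status.

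The planned fallbacks in the same scenario:
- Nonresponders as vapers: app 6.57%, control 0.0802 × 0.75 = 6.02% (6.574 − 6.015), difference +0.56 points.
- Last observation carried forward: app 0.08 × (0.60 × 0.90 + 0.10) + 0.0322 × 0.70 = 7.37%; control 0.08 × (0.60 × 0.75 + 0.25) + 0.0322 × 0.75 = 8.02%; difference −0.64 points.

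**5. Simulation for a 3-month outcome.** Assumed parameters, 400,000 people, about 5% against 9% abstinent, 73% to 75% response. The named-type model was simplified to arm plus a dependence score. The last column adds baseline use, 6-month status observed for everyone, and an arm-by-status term. Risk differences in points:

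| Response depends on | True | Named-type | + baseline use | + use and other wave |
|---|---|---|---|---|
| Dependence only | 3.49 | 3.52 | 3.52 | 3.49 |
| Dependence and baseline use | 3.81 | 3.89 | 3.81 | 3.78 |
| Also on quitting, both arms | 3.66 | 4.00 | 3.95 | 3.62 |
| Also on quitting, app arm only | 3.64 | 4.56 | 4.50 | 3.62 |

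Bias of the named-type model: 0.03, 0.08, 0.34 and 0.92 points. Adding the other wave's status brings the last two to within 0.04 of the truth.

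**6. Quitters available.** At 225 responders per arm: 0.05 × 225 ≈ 11 in controls and 0.0777 × 225 ≈ 17 in the app arm.

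**The case against.** **The list may be open.** It says what the model will include and does not say that nothing else enters. The sentence before it would admit other-wave status as an observed predictor, and a condensed article can leave auxiliary variables to the analysis plan. This stands in part: the omission is not proof that these variables will be excluded. But the article chose to name variables, and naming province and marital status while leaving out other-wave status invites either omission or a later choice.

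**A reader might infer that the model cannot correct dropout bias.** The document does not support that. Dependence, self-confidence, stress and arm are named, and in the first row of the simulation the named-type model is out by only 0.03 points.

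**A reader might infer that the fallback analyses are useless.** That fails as well. They coincide only at month 3. In the 6-month scenario of step 4 they give +0.56 and −0.64 points, on either side of the true zero, and so would cast doubt on a spurious +1.2.

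**The two parts lean on different time points.** Imputing month 6 from month 3 presumes a 6-month outcome, while identical fallbacks presume a 3-month one. This is fair and follows from the protocol's own conflict. At month 3 only later waves can help, and people who never respond again have none.

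**The size is assumed.** The document says nothing about response by quit status or arm, and the largest figures put the whole imbalance in the app arm, in the app's favour. This stands in full.

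**Conclusion.** The point holds as a gap in the named list. Followed as written, the imputation model may leave bias when response depends on vaping status; dropout explained by the named variables is handled.

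The illustrations give about 0.3 points (quitters respond more in both arms), 0.9 points (app arm only, month 3) and 1.2 points (app arm only, month 6), against a planned 2.77. They show direction and rough scale and are not forecasts. The corrections to near zero assume that the other wave's status is observed for everyone, so in practice adding it would reduce the bias rather than remove it.

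The point about the fallbacks is conditional. With a 3-month primary outcome, Secondary Outcomes supplies one sensitivity analysis under several names. With a 6-month outcome it supplies two that differ.

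**What to change.** 1. Reconcile the primary time point, since it decides whether the fallbacks coincide.
2. Add to the named imputation variables 30-day vaping status at all other follow-up waves, baseline e-cigarette use and smoking status. Keep arm in the model.
3. Collapse or drop sparse categories such as province and marital status. Fit separately by arm only if the number of quitters allows; with about 11 expected among control responders it may not.
4. Keep the nonresponder-as-vaper analysis as one sensitivity analysis. Where the two approaches coincide, replace last observation carried forward with a delta-adjusted imputation that lowers the odds of abstinence in nonresponders over a range stated in advance. This also covers people with no later response, whom the added variables cannot help.

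**Cost.** Some wording and a little programming; no new data collection. The downside is possible instability of a larger model with few quitters, which step 3 is meant to limit.

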## Discussion

### Protocol Overview

This is the first-ever RCT study to evaluate the effectiveness of a smartphone app for supporting youth vaping cessation. The primary aim of our study is to determine the effectiveness of the *Crush the Crave* app in supporting vaping cessation among youth recruited to the intervention arm via comparison with an assessment-only control group. The primary hypothesis is that participants in the intervention group—those using *Crush the Crave*—will be more likely to be abstinent at the 6-month follow-up point than participants in the assessment-only control arm.

The *Crush the Crave* app was developed based on the best available evidence on vaping cessation and an empirical investigation on the effectiveness of an earlier version of the app for smoking cessation [22]. At the time of writing, 4 other clinical trial protocols for evaluating vaping cessation interventions among youth and young adults were registered on ClinicalTrials.gov. Of these, only 1 has been completed; the results are accessible in the published scientific literature and show that the intervention was successful (abstinence success rates of 16% for the intervention group and 8% for the control group) in encouraging young adults to stop vaping through an SMS text messaging program [8]. This study was useful in providing a benchmark for intervention effectiveness [8]. Of the 3 remaining protocols that are actively recruiting participants, 2 aim to evaluate the effectiveness of nicotine replacement therapy for vaping cessation among youth and young adults, and 1 aims to determine the effectiveness of a smartphone app called *Goal2QuitVaping*. Compared to the target sample size in our study (N=600), that of the Goal2QuitVaping study is relatively small (N=45).

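### The sample of 600 does not give 80% power for an odds ratio of 1.60 at a 5% base rate; with 450 analysed the power is about 22% (two-sided)

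*Protocol article*

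**What the plan says.** The only justification for the sample size is in Methods, Data Analysis Plan, Primary Outcome. The total is given for both arms together ("The sample size of 600 (inclusive of both the control arm and the intervention arm"), and was "selected to differentiate an effect size odds ratio of 1.60, assuming a base cessation rate of 5%, an α of .05", with "a power of 0.8, and a 75% (450/600) response rate". Trial Design splits the 600 as 300 per arm, 1:1. The outcome is binary: 30-day point prevalence abstinence. The statement does not say whether alpha is one-sided or two-sided. It names no formula and claims no gain in power from covariates or repeated measures.

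The same section plans multiple imputation of missing outcomes, with everyone analysed as randomised. The Discussion (Protocol Overview) cites one completed vaping cessation trial as a benchmark, with "abstinence success rates of 16% for the intervention group and 8% for the control group".

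**The concern.** A 5% event rate yields few events: about 11 in the control arm if 225 are analysed. An odds ratio of 1.60 adds only about six more in the intervention arm. A difference that small cannot normally be detected with 80% power in 450 people, so the stated power looked far too high.

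Funders, ethics boards and readers rely on this statement to judge what the trial can show. If the true power is a fraction of 80%, a non-significant result is the likely outcome even when the app works as well as assumed. With 80% power on record, that result could be taken as evidence that the app does not work. A null finding is a realistic prospect: the Introduction reports that the earlier smoking version of the app showed no significant difference from control.

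**Working it through.** **Inputs**, all from Data Analysis Plan, Primary Outcome, except the allocation (Trial Design): N = 600, 1:1; odds ratio 1.60; base rate p1 = 0.05; alpha .05; power 0.80; response 75%, so 450 analysed, 225 per arm. Sidedness is not stated, so both are shown.

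**Implied intervention rate.** The control odds are 0.05/0.95 = 0.05263. Multiplying by 1.60 gives 0.08421, so p2 = 0.08421/1.08421 = 0.0777. The difference is 0.0277, a number needed to treat of about 36. Expected events at 225 per arm: 225 × 0.05 ≈ 11 and 225 × 0.0777 ≈ 17.

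**Attempt to reproduce the stated 0.80.** Two-proportion test with pooled variance under the null:

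power = Φ{ [ (p2 − p1)√n − z√(2p̄(1 − p̄)) ] / √(p1(1 − p1) + p2(1 − p2)) }

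Here p̄ = 0.0638, √(2p̄(1 − p̄)) = 0.3457 and the denominator is 0.3452. With n = 225 and z = 1.96:

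(0.02767 × 15 − 1.96 × 0.3457)/0.3452 = (0.4150 − 0.6776)/0.3452 = −0.761, and Φ(−0.761) = **0.223**.

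Other methods agree: Wald test on the log odds ratio 22.1%, exact power of the chi-square test 21.9%, Fisher's exact test 17.2%, and a chi-square simulation with 200,000 runs 22.0%.

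**Other readings of the statement:**

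| Reading | Two-sided | One-sided |
|---|---|---|
| 225 per arm (as stated) | 22.3% | 32.8% |
| 300 per arm, complete data | 28.3% | 39.8% |
| 450 taken as per arm | 39.6% | 52.1% |
| 600 taken as per arm | 50.0% | 62.4% |
| 1.60 as a risk ratio (5% vs 8%), 225 per arm | 25.1% | 36.1% |
| 1.60 as a risk ratio, 600 per arm | 55.9% | 67.9% |
| Nonresponders counted as vapers, 300 per arm | 22.1% | 32.5% |

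A mistyped base rate does not explain it under a two-sided test either. With odds ratio 1.60 and 225 per arm, two-sided power peaks at about 70%, near a 44% base rate.

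**Size needed for 80% two-sided power:**

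n = [1.96 × 0.3457 + 0.8416 × 0.3452]² / 0.02767² ≈ **1,225 per arm** (1,296 with continuity correction).

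That is 2,450 analysed, and 2,450/0.75 ≈ 3,270 randomised. One-sided: 965 per arm, 1,930 analysed, about 2,574 randomised.

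**What the planned size can detect (80% power, two-sided, base rate 5%):** odds ratio 2.70 (5.0% vs 12.4%) at 225 per arm; odds ratio 2.40 (5.0% vs 11.2%) at 300 per arm.

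**Benchmark rates.** 8% vs 16% is an odds ratio of (0.16/0.84)/(0.08/0.92) = 2.19. Two-sided power is 74% at 225 per arm and 86% at 300. At an 8% base rate with odds ratio 1.60, it is 32% at 225 per arm.

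**Precision.** The 95% half-width for the risk difference at 225 per arm is 1.96 × √[(0.05 × 0.95 + 0.0777 × 0.9223)/225] ≈ 0.045. That is 4.5 points, wider than the 2.77-point target.

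**The case against.** The strongest reply is that the paragraph shows only that five numbers do not fit together, not which of them is wrong. The odds ratio, the base rate or the method may be at fault and the power intended. For instance, the logistic regression formula for a standardised continuous predictor, (z_α + z_β)²/[p(1 − p)(ln OR)²], gives 589 in total one-sided and 748 two-sided. The one-sided figure is close to 600. That formula is not valid for a two-arm comparison and leaves no room for 75% response, and its use here is conjecture. The point that the source of the error is unknown does stand, and the fix allows for it.

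Second, sidedness is not stated, so 22% is conditional on a two-sided test. That is fair, but one-sided power is still only 33%.

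Third, the primary analysis imputes missing outcomes and keeps all 600, so a calculation on 225 per arm may be pessimistic. Imputation cannot recover more than complete data would hold, and complete data give 28% two-sided. For the benchmark rates this matters more: power lies between 74% and 86%, depending on how informative the imputation is.

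Fourth, planning for a smaller effect than the benchmark trial found is legitimate. Agreed; the finding does not rest on that comparison.

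Finally, a published article condenses a fuller protocol. That excuses omissions, but this is a complete statement whose parts contradict one another.

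**Conclusion.** The stated power is wrong for the stated inputs. For odds ratio 1.60 at a 5% base rate, 450 analysed give about 22% power (two-sided alpha .05, unadjusted comparison of two proportions, 225 per arm). Complete follow-up raises this to 28%, and a one-sided test at 225 per arm gives 33%. The most favourable misreading tried, a risk ratio of 1.60 with 600 per arm and a one-sided test, stops at 68%. The shortfall is more than fivefold: 2,450 analysed are needed against 450 planned. No gain from covariates is claimed, and none plausible for a rare binary outcome would close that gap. The size of 600 can be defended for a larger effect, but not for the one named. This must be corrected.

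**What to change.** Keep 600 and rewrite the sample size paragraph. The sponsor should first go back to the original calculation and establish whether the odds ratio, base rate or method was misreported, then correct that element and state the sidedness of alpha. If the inputs are as intended, wording such as this would do:

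> With 450 of 600 participants analysed, the trial has 80% power (two-sided alpha .05) to detect an odds ratio of 2.7 at a 5% base rate (5.0% versus 12.4%), and 74% power for 8% versus 16% (86% if all 600 provide data). Power for an odds ratio of 1.60 at a 5% base rate is about 22%. A non-significant result will be interpreted from the confidence interval for the risk difference and not as evidence of no effect.

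The cost is one reworded paragraph and a less favourable power statement. It needs no additional participants and no change to the analysis.
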